### 9.3. Analyses Supporting the Primary Objective

#### 9.3.1. Primary Endpoint

The primary endpoint shall be the change from baseline in CFT at week 1.

##### 9.3.1.1. Definition of the Endpoint

- Change: The change from baseline shall be calculated using the following formula.  
Change = measurement at week 1 – baseline value

#### 9.3.2. Primary Analysis Method

For CFT, the 95 % confidence interval of the mean change from baseline at week 1 will be calculated, and a significance test will be performed using a t-test.

Intercurrent events shall be handled as follows.

For vitreous re-surgery for ocular-complication treatment, sub-Tenon injection of triamcinolone acetonide, rescue therapy with photodynamic therapy or VEGF inhibitors, and the administration of prohibited concomitant therapy for other diseases such as defibrotide sodium or tPA preparations (including monteplase) (adopting a treatment policy strategy approach), all observed values of the primary endpoint shall be used in the analysis. For withdrawal of consent or loss to follow-up not due to serious adverse events, intravitreal gas injection as rescue therapy, and the administration of prohibited tPA preparations (including monteplase) as additional treatment for sub-macular hemorrhage (adopting a hypothetical strategy approach), data collected after the occurrence of the intercurrent event shall be excluded from the analysis in order to evaluate the treatment effect without these influences. For vitreous re-surgery due to re-bleeding, withdrawal of consent due to serious adverse events, and hematoma-removal surgery using prohibited concomitant therapy (adopting a composite strategy), the change value of 0 shall be imputed as the worst value for the primary endpoint in cases where the intercurrent event occurred, and these cases shall be analyzed accordingly.

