| Withdrawal of consent / loss to follow-up                                       |                                                                                                                 | Withdrawal of consent for reasons that have a major impact on the evaluation items (e.g., serious adverse events) | Composite variable             | Composite variable             | Composite variable              | Composite variable                               | Composite variable             | Composite variable | Composite variable              | Composite variable                                                        |
|                                                                                 |                                                                                                                 | Withdrawal of consent or loss to follow-up for reasons other than those described above                           | Virtual                        | Virtual                        | Virtual                         | Virtual                                          | Virtual                        | Virtual            | Virtual                         | Virtual                                                                   |
| Implementation of rescue therapy                                                | Photodynamic therapy                                                                                            | Treatment of underlying disease                                                                                   | Treatment policy               | Treatment policy               | Treatment policy                | Treatment policy                                 | Treatment policy               | Treatment policy   | Treatment policy                | Treatment policy                                                          |

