##### 7.2. Subject Discontinuation/Withdrawal

The trial for a subject shall be discontinued if any of the following applies:

- 1) The subject withdraws consent (the detailed reason for withdrawal shall be recorded in the case report form).
- 2) The subject is found to be ineligible after enrollment.
- 3) Based on a comprehensive safety assessment, including the occurrence of adverse events, the principal investigator or sub-investigator judges that continuation of the trial is infeasible (the detailed reason for infeasibility shall be recorded in the case report form).
- 4) The subject dies.
- 5) After trial initiation it becomes evident that, due to the subject's circumstances, required subsequent examinations or observations cannot be performed.
- 6) The subject meets the definition of loss to follow-up as defined in Section 7.3.
- 7) Any other situation in which the principal investigator or sub-investigator judges continuation of the trial to be infeasible (the detailed reason for trial discontinuation shall be recorded in the case report form).

At the time of discontinuation, appropriate medical care shall be provided based on the physician's judgment. To the extent feasible, the observations and examinations specified in the protocol for trial discontinuation shall be performed to evaluate safety. If the trial is discontinued because of an adverse event, the event shall be classified according to Section 10.2.3 (outcome categories 1, 4, 5) and follow-up of the adverse event shall be conducted up to 28 days after discontinuation. If follow-up cannot be performed, the reason shall be documented in the case report form. No discontinuation assessments shall be performed

for discontinuations that occur prior to any trial intervention.

A subject may withdraw from the trial at any time, for any reason or without providing a reason, upon the subject's own request, and no disadvantage shall result. Even if a subject withdraws consent, data collected prior to withdrawal shall, in principle, be included in the analysis set.

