#### 9.1.4. Handling of Missing Data

The handling of missing data shall be described in detail in the Statistical Analysis Plan.

Except as specified in the Statistical Analysis Plan, missing values shall not be imputed as a general principle.

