- ✓ The lack of efficacy or the absence of the expected pharmacologic effect is not reported as an AE. These examples are described in the efficacy evaluation.

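### Section 9.3.2 counts only withdrawal due to serious adverse events as failure, while Table 3-1 counts withdrawal for any reason with a major impact on the endpoint

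*Protocol*

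**What the plan says.** The protocol sets the boundary between failure and exclusion for withdrawals in two places.

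- **Table 3-1 (section 3).** The composite row reads "Withdrawal of consent for reasons that have a major impact on the evaluation items (e.g., serious adverse events", where the bracket gives an example and not a limit. The row below it, "Withdrawal of consent or loss to follow-up for reasons other than those described above", is marked virtual, which is the hypothetical strategy of 9.1.3. The same strategies apply in every endpoint column, including Week 1 CFT.
- **Section 9.3.2.** The composite group contains only "withdrawal of consent due to serious adverse events", alongside re-operation for re-bleeding and hemorrhage-removal surgery. For this group "the change value of 0 shall be imputed as the worst value for the primary endpoint". The hypothetical group opens with "For withdrawal of consent or loss to follow-up not due to serious adverse events", and its post-event data are left out.

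Three other places bear on the point:

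- Section 9.1.3 reserves the composite strategy for events regarded as clinical treatment failure and assigns them a value of no improvement.
- Section 10.2.1 states: "The lack of efficacy or the absence of the expected pharmacologic effect is not reported as an AE".
- Section 9.1.4 leaves missing data to the SAP and, apart from what the SAP specifies, says that "missing values shall not be imputed as a general principle".

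**The concern.** Both rules govern the same endpoint, and no SAP can follow both. They disagree on withdrawals for a reason that weighs heavily on the outcome but is not a serious adverse event. The clearest case is a subject who leaves because the treatment has not worked. Table 3-1 treats that subject as a failure; 9.3.2 treats the subject as if the withdrawal were unrelated to outcome.

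The disagreement has a direction. The subjects whom 9.3.2 leaves out and Table 3-1 keeps are likely to be those doing badly, so following 9.3.2 makes the mean CFT reduction look larger. In an open-label, single-arm trial of 20 subjects the estimated mean change is a main product, and a rule that depends on how a withdrawal reason is worded should be fixed in advance and in one form.

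**Working it through.** **1. The two rules side by side, for a subject who withdraws consent before the Week 1 measurement**

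| Reason for withdrawal | Table 3-1 | Section 9.3.2 |
|---|---|---|
| Serious adverse event | Composite, change = 0 | Composite, change = 0 |
| Major-impact reason that is not a serious adverse event, such as lack of effect | Composite, change = 0 | Hypothetical, post-event data excluded |
| Any other reason | Hypothetical | Hypothetical |

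Only the middle row conflicts.

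**2. Can lack of effect still reach the composite group in 9.3.2?** No. Section 10.2.1 does not let it be reported as an adverse event, so by itself it cannot be a serious one.

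**3. What happens to that subject under 9.3.2?** Section 9.3.1.1 defines the change as the Week 1 value minus baseline. Without a Week 1 value there is no change score, and by the default in 9.1.4 nothing replaces it unless the SAP says so. The subject gives no value to the t-test. A subject who leaves after the Week 1 measurement keeps it: 9.3.2 excludes only later data, and 7.2 in principle keeps data collected before withdrawal.

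**4. The plan's own figure (9.9).** Inputs: mean −120 µm, SD 170 µm, effect size 0.7, two-sided 5 %, 80 % power. With the noncentral t distribution and d = 0.70, n = 18 gives power 0.7992 and n = 19 gives 0.8225, so 19 is reproduced. Then 19 / 0.95 = 20. The sample size is not affected by this point.

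**5. Size of the conflict.** The protocol gives no rate of such exits, so k of 20 is an assumption. The remaining 20 − k subjects are taken to have mean −120 µm and SD 170 µm.

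- Dropped (9.3.2): expected mean = −120.
- Scored 0 (Table 3-1): expected mean = −120 × (20 − k) / 20.

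| k | Mean if dropped (µm) | Mean if scored 0 (µm) | Power if dropped | Power if scored 0 |
|---|---|---|---|---|
| 1 | −120 | −120 × 19/20 = −114 | 0.829 | 0.829 |
| 2 | −120 | −120 × 18/20 = −108 | 0.808 | 0.807 |
| 3 | −120 | −120 × 17/20 = −102 | 0.781 | 0.779 |
| 4 | −120 | −120 × 16/20 = −96 | 0.752 | 0.749 |

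The powers come from 100,000 simulated trials per row. Each affected subject moves the mean by 120 / 20 = 6 µm, or 5 %. With 19 subjects analysed the standard error is 170 / √19 = 39.0 µm, so one such subject shifts the estimate by 6 / 39.0 = 0.15 standard errors. Power differs by about 0.003 at most.

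**The case against.** The strongest reply is that this will rarely matter. Only exits before the Week 1 measurement (Day 8, window −1 to +3) count, and the schedule shows hospitalization over the treatment-period visits. The dropout allowance in 9.9 is 5 %, or 0.05 × 20 = 1 subject from all causes. One reclassified subject is well inside sampling error. All of this stands and limits the size of the point. It does not reconcile the two texts.

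A second reply is that Table 3-1 never defines a major impact, so lack of effect is a reading. That is fair. The reading rests on 9.1.3, which ties the composite strategy to treatment failure. Treating every withdrawal for a non-serious adverse event as a failure under Table 3-1 would go further than the text allows.

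A reader might also infer stronger claims that the protocol does not support:

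- **That 9.3.2 deletes every subject who withdraws for another reason.** It excludes only post-event data.
- **That subjects stopped by the investigator, and deaths, are lost through this mismatch.** Section 7.2 lists separately from consent withdrawal the case where "the principal investigator or sub-investigator judges that continuation of the trial is infeasible", and also death. Neither the withdrawal rows of Table 3-1 nor 9.3.2 names them, so aligning the two would not change their handling. Section 9.1.3 presents the table as the events anticipated at the start, and the rest may be left to the SAP.
- **That the protocol forbids imputation.** Section 9.1.4 defers to the SAP.
- **That worsening can never count as failure under 9.3.2.** Section 10.2.1 treats worsening symptoms of the underlying disease as an adverse event, and 8.4.7 has re-bleeding assessed for that status. If serious, it meets the 9.3.2 wording. Plain non-improvement does not.
- **That primary and secondary endpoints will be handled differently.** Table 3-1 uses the same strategies at Weeks 4 and 12, but 9.4.1 gives no intercurrent-event rules, so this is open.

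**Conclusion.** The protocol is wrong as written on this point: it fixes two incompatible boundaries for its primary endpoint, and 9.3.2 leaves out some withdrawals that its own estimand scores as failures. The consequence is a small bias toward benefit, 6 µm (5 %) per affected subject, with practically no effect on power.

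This rests on five assumptions: lack of effect counts as a major-impact reason; the exit comes before the Week 1 measurement; the SAP does not impute the value; the subject is otherwise in the FAS, which excludes anyone without post-dose efficacy data; and one or two of 20 subjects are affected, a number the protocol does not supply.

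**What to change.** Reword 9.3.2 to use the Table 3-1 boundary:

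- **Composite (change of 0):** withdrawal of consent for a reason strongly affecting the evaluated outcomes, stated to include serious adverse events and lack of effect.
- **Hypothetical:** withdrawal of consent or loss to follow-up for other reasons only.

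Classify the recorded withdrawal reasons before database lock. Section 7.2 already requires the detailed reason in the case report form, so no new data are needed.

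Narrowing Table 3-1 to match 9.3.2 would also remove the contradiction. It fits 9.1.3 less well, because withdrawal for lack of effect would then not count as treatment failure.

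The cost is a wording change. The downside is that the estimated mean reduction may be slightly less favourable. Investigator-decided discontinuation and death are a separate matter that the SAP can settle.

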##### 9.3.2.1. Sensitivity Analysis

For CFT, the significance of the change from baseline at week 1 shall be tested using the Wilcoxon signed-rank test.

The Wilcoxon signed-rank test is a non-parametric test that does not assume the change follows a normal distribution and will be performed as a sensitivity analysis.

#### 9.3.2.2. Supplemental Analysis

In addition to the primary and sensitivity analyses, for cases in which intercurrent events occur multiple times or serious adverse events occur multiple times, the number of occurrences will be identified and the relationship with the primary endpoint will be analyzed.

Furthermore, considering the pure pharmacologic effect of the investigational product after excluding the influence of VEGF-inhibitor use or tPA-preparation use for other diseases, and recognizing that this is important for the treating physician's clinical decision-making for each patient, an evaluation will be performed assuming a virtual strategy in which the intercurrent events of VEGF-inhibitor use and the use of montepase or other tPA preparations for other diseases are assumed not to have occurred. Specifically, data collected after the occurrence of the intercurrent event will be excluded, and the analysis will be conducted in the same manner as the primary analysis.

### 9.4. Analyses Supporting Secondary Objectives

#### 9.4.1. Analyses Supporting Secondary Objectives

##### 1) Change from baseline in CFT at week 4

For CFT, the 95 % confidence interval of the mean change from baseline at week 4 will be calculated, and a significance test will be performed using a t-test.

##### 2) Presence of a foveal hemorrhage $\geq 1$ disc diameter at week 4

The proportion of subjects with a foveal hemorrhage  $\geq 1$  disc diameter at week 4 will be evaluated for significance using a chi-square test.

##### 3) BCVA (logMAR equivalent) at week 4

For BCVA (logMAR equivalent), the 95 % confidence interval of the mean at week 4 will be calculated.

##### 4) Change from baseline in BCVA (logMAR equivalent) at week 4

For BCVA (logMAR equivalent), the 95 % confidence interval of the mean change from baseline at week 4 will be calculated, and significance will be tested using a t-test.

##### 5) Change from baseline in CFT at week 12

For CFT at week 12, the 95 % confidence interval of the mean change from baseline will be calculated, and significance will be tested using a t-test.

##### 6) BCVA (logMAR equivalent) at week 12

For BCVA (logMAR equivalent), the 95 % confidence interval of the mean at week 12 will be calculated.

##### 7) Change from baseline in BCVA (logMAR equivalent) at week 12

For BCVA (logMAR equivalent), the 95 % confidence interval of the mean change from baseline at week 12 will be calculated, and significance will be tested using a t-test.

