| i. Treatment condition of interest | Subretinal administration of monteplase (recombinant)                                                                                                                                                                                                                                                               |
| ii. Population                     | Patients with SMH defined by the inclusion criteria (severe sub-macular hemorrhage in which spontaneous resolution is not expected, the bleed involves the fovea, and marked visual-acuity loss is anticipated)                                                                                                     |
| iii. Endpoint                      | 1) Change in CFT from baseline at Week 4.
2) Presence or absence of a foveal hemorrhage measuring $\geq 1$ disc diameter at Week 4.
3) BCVA (logMAR equivalent) at Week 4.
4) Change in BCVA (logMAR equivalent) from baseline at Week 4.                                                                  |
| iv. Other intercurrent events      | See Table 3-1                                                                                                                                                                                                                                                                                                       |
| v. Population-level summary        | 1) Mean change from baseline to Week 4 in CFT measured by OCT.
2) Proportion of patients with foveal hemorrhage measuring $\geq 1$ disc diameter observed by fundus photography at Week 4.
3) Mean BCVA (logMAR equivalent) at Week 4.
4) Mean change from baseline to Week 4 in BCVA (logMAR equivalent). |

Rationale for the estimand: SMH causes acute and severe visual impairment, and prolonged hemorrhage may induce irreversible degeneration of the neurosensory retina, thereby affecting visual prognosis. Even when considering the effects of VEGF inhibitor use after monteplase administration or the use of tPA products for other diseases, reduction of the hematoma,

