#### 4. Study Design

##### 4.1. Overview of Study Design

Intervention Model: Single-group

Control: Baseline control

Active Comparator: None

Allocation Method: None

Masking: None

Target Population Type: Adult subjects

Target Population Diagnosis: SMH secondary to AMD or RAM

Target Population Age Range: Minimum 18 years, no upper limit

Distribution of Study Sites: Multicenter collaborative

Trial Phase: Phase II

Committee: None

Duration of Participation per Subject: 12-week observation period after enrollment

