#### 4.2. Rationale for Study Design

##### <Single-Group Trial>

The natural course of SMH varies according to hematoma volume and location of bleeding. Small hematomas or hemorrhages that do not involve the fovea may resolve spontaneously with minimal impact on visual acuity. In this study, we will enroll severe patients in whom a large hematoma is unlikely to resolve spontaneously and whose bleeding involves the fovea, resulting in a predicted marked loss of visual acuity. The study will therefore be a pre-post comparison trial evaluating objective measurements reflecting hematoma volume and visual function before and after tPA administration. In the patient population targeted by this trial, improvement of the disease state is not expected with no treatment, vitrectomy with gas tamponade, or vitrectomy with oil tamponade; consequently, establishing a control arm would be ethically unacceptable. Moreover, sub-retinal administration of a placebo could cause complications such as retinal detachment, rendering a placebo arm ethically unacceptable. Accordingly, the trial will be conducted without a control group as an open-label, single-arm study of the investigational product.

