#### 5.1. Inclusion Criteria

Subjects are eligible to participate in this trial only if they meet all of the following criteria:

Age:

- 1) Patient aged  $\geq 18$  years at the time of signing the informed consent form.

Disease Characteristics:

- 2) Patient with sub-macular hemorrhage involving the fovea secondary to AMD or RAM in the study eye.

- 3) At screening, CFT measured by OCT in the study eye is  $\geq 300 \mu\text{m}$ .
- 4) At screening, BCVA in the study eye is  $\leq 0.2$  (decimal).

Other:

- 5) Patient who can provide written informed consent; if visual impairment makes document review difficult, verbal consent may be obtained from the subject together with the signature of a witness.
- 6) (For women of child-bearing potential) Patient who, from the time informed consent is obtained until 2 days after investigational product administration, agrees to use an appropriate method of contraception\*.

\* See 10.3.2.

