#### 9.1. General Considerations

##### ● Baseline Definition

Baseline assessments or events are defined as assessments or events that occurred prior to the date and time of administration of the investigational product. When multiple valid assessments or events are available, the assessment closest to the investigational product administration date (and time, if collected) shall be used as the baseline for analysis.

- Summary Statistics

For continuous variables, summary statistics shall include the number of observations, mean, standard deviation, minimum, median, maximum, first quartile (25th percentile), and third quartile (75th percentile). For categorical variables, summary statistics shall include the number of observations and the frequency and percentage (%) of each category.

Means, standard deviations, medians, first quartiles, and third quartiles shall be rounded to two decimal places and displayed to one decimal place. Minimum and maximum values shall be rounded to one decimal place and displayed to the specified number of digits. Percentages (%) and the upper and lower limits of their confidence intervals shall be rounded to the second decimal place and displayed to one decimal place.

- Significance Level and Confidence Coefficient

Unless otherwise specified, the significance level for hypothesis testing shall be two-sided 5 %. For interval estimation, unless otherwise stated, two-sided intervals shall be used with a confidence coefficient of 95 %. P-values shall be rounded to the fourth decimal place and displayed to three decimal places; however, if the unrounded p-value is less than 0.001, it shall be uniformly reported as "<0.001".

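### A chi-square test is prescribed for a single Week 4 proportion in a one-arm trial, with no null proportion and no comparison stated

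*Protocol*

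**What the plan says.** Protocol Section 9.4.1, item 2, concerns foveal hemorrhage of at least 1 disc diameter. Its whole analysis is that the proportion with such a hemorrhage of at least 1 "disc diameter at week 4 will be evaluated for significance using a chi-square test". No null value, comparison group or interval is given for it.

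Other sections set the context:

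- **Design (Section 4.1).** "Intervention Model: Single-group", "Control: Baseline control", "Active Comparator: None". Section 4.2 adds: "The study will therefore be a pre-post comparison trial".
- **Population-level summary (Section 3, estimand for secondary objective 1).** This is the proportion of patients with the finding "observed by fundus photography at Week 4". It is one time point, not a change.
- **Eligibility (Section 5.1, item 2).** "Patient with sub-macular hemorrhage involving the fovea secondary to AMD or RAM in the study eye". Item 3 adds a CFT threshold. Neither sets a minimum hemorrhage size in disc diameters.
- **Error level (Section 9.1).** "Unless otherwise specified, the significance level for hypothesis testing shall be two-sided 5" %. Section 9.1.2 applies no multiplicity adjustment.
- **Stated hypotheses (Section 9.1.1).** The only null hypothesis is for the Week 1 change in CFT.

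**The concern.** A significance test needs a null value or a second sample, and item 2 supplies neither. It also stands apart from the rest of Section 9.4.1. The tested continuous endpoints (items 1, 4, 5 and 7) are changes from baseline, for which zero is a natural null. The other single-time-point endpoints, BCVA at Weeks 4 and 12 (items 3 and 6), get a 95% confidence interval and no test. Item 2 is the only single-time-point value that is tested, and the only secondary efficacy item for which no interval is requested.

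At stake is a p-value, read at a nominal 5%, that answers no question of the trial or that depends on a comparison chosen when the analysis is programmed. In addition, because eligibility does not require the finding at baseline, a Week 4 proportion alone can count as favourable an eye that never had it.

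**Working it through.** **Inputs.** N = 20 (Section 9.9) and two-sided 5% (Section 9.1). The protocol gives no expected rate and no figure of its own for this endpoint, so there is nothing to reproduce. The counts below are assumptions, with all 20 subjects evaluable.

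**Reading 1: one-sample chi-square with no stated null.** The usual default is equal frequencies, so 10 with and 10 without the finding are expected. With x subjects having the finding,

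X² = (x − 10)²/10 + ((20 − x) − 10)²/10, on 1 degree of freedom.

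| With hemorrhage at Week 4 | X² | p |
|---|---|---|
| 5/20 | 2.5 + 2.5 = 5.0 | 0.025 |
| 10/20 | 0 | 1.00 |
| 15/20 | 2.5 + 2.5 = 5.0 | 0.025 |

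Persistence in 75% of eyes is exactly as significant as persistence in 25%. If all 20 eyes had the finding at baseline and half cleared, p would be 1.00. The p-value measures distance from 50%, not benefit.

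**Reading 2: baseline against Week 4, treated as two independent samples.** The same eyes are measured twice, so the valid test uses only the eyes that change. With k eyes clearing and none newly positive, McNemar's chi-square is k²/k = k, and the exact two-sided p is 2 × 0.5^k. Asymptotic tests are compared with asymptotic, and exact with exact, so that the contrast reflects pairing and not the choice of approximation.

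| Baseline → Week 4 (none new) | Pearson, unpaired | McNemar chi-square | Fisher, unpaired | Exact McNemar |
|---|---|---|---|---|
| 20/20 → 15/20 (k = 5) | 0.017 | 0.025 | 0.047 | 0.063 |
| 20/20 → 16/20 (k = 4) | 0.035 | 0.046 | 0.106 | 0.125 |
| 14/20 → 8/20 (k = 6) | 0.057 | 0.014 | 0.111 | 0.031 |

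Arithmetic for the first and last rows:

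- 20 → 15: Pearson X² = 40 × (20×5 − 0×15)² / (20×20×35×5) = 5.71. Exact McNemar = 2 × 0.5⁵ = 0.0625.
- 14 → 8: Pearson X² = 40 × (14×12 − 6×8)² / (20×20×22×18) = 3.64. Exact McNemar = 2 × 0.5⁶ = 0.031.

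In the first row the unpaired exact test is below 5% and the paired one is not. In the second row the conclusions agree within each method. In the third row the unpaired test misses a difference that the paired test finds, by either method. Ignoring the pairing can therefore err in either direction.

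**Reading 3: estimation.** The exact (Clopper-Pearson) 95% interval for 5/20 is 8.7% to 49.1%. It needs no null value.

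**The case against.** The strongest reply is that the wording is merely terse. McNemar's test is itself a chi-square test, the trial is declared baseline-controlled and pre-post, and the protocol writes only t-test for the continuous endpoints without saying paired or one-sample. Section 9 leaves technical detail to a statistical analysis plan that is not at hand. On this view a valid paired test may be what is meant.

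Part of this stands. A reader might infer that the analysis must be one of two wrong tests, against 50% or unpaired. The protocol does not support that: a paired McNemar test, or a test against a reference rate stated elsewhere, is also compatible with the words.

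The reply does not remove the point. For the continuous endpoints the change from baseline is in the endpoint definition, so the null is evident. Here the endpoint and its population summary are a Week 4 value only. Which proportion is compared with what is the hypothesis itself, not technical detail, and the protocol has already fixed the test.

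A second reply is that this is one of seven secondary efficacy endpoints in a study that Section 4.2 calls exploratory. That is correct and limits the weight of the point.

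**Conclusion.** Item 2 is wrong as written: it prescribes a significance test for one proportion without a null value or a comparison. Followed literally, it yields a p-value that treats 5/20 and 15/20 alike (p=0.025 for both). If baseline against Week 4 is intended, only a paired test is valid, and the text does not name one.

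Two stronger inferences should be avoided. One is that an unpaired test would always overstate significance; the 14/20 to 8/20 case runs the other way. The other is that setting Pearson 0.017 against exact McNemar 0.063 shows the cost of ignoring pairing. That contrast mixes an asymptotic with an exact test; like for like it is 0.017 against 0.025, or 0.047 against 0.063.

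All p-values rest on assumed counts with 20 evaluable subjects and no newly positive eyes. The defect itself does not depend on them. The effect is confined to one secondary endpoint; the primary CFT analysis and the sample size, which rests on CFT alone, are unaffected.

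**What to change.** Delete the chi-square test from Section 9.4.1, item 2, and report the Week 4 proportion with an exact two-sided 95% confidence interval. This matches the Section 3 summary and the treatment of BCVA in items 3 and 6.

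If a pre-post test is wanted, state that comparison in Sections 3 and 9.4.1 and use the exact McNemar test on the paired screening and Week 4 fundus-photograph gradings. If every eye proves positive at baseline, that test only counts clearances and adds little to the interval. Because eligibility does not guarantee the finding at baseline, also show the baseline proportion and, as a description, clearance among eyes positive at baseline.

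The cost is protocol and analysis-plan wording. No new data are needed: fundus photography is scheduled at screening and Week 4 (Section 1.3) and is graded for this finding (Section 8.2.2). Adding the pre-post comparison would extend the estimand beyond its present single proportion, so it should be written as a deliberate change.
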